#### Five bi-weekly telephone consultation sessions

To reduce time in traveling and to increase motivation and adherence to behavioral change recommendations, the telephone consultation will occur one week after each in-person meeting. Five telephone consultation sessions of ILSM program include: 1) review of progress toward dietary, physical activity and goals, 2) identify challenges faced in achieving goals, 3) assist with setting new action plans and achievable goals, and 4) encourage achievement of goals.

#### Three monthly telephone consultations at the maintenance phase

After the intensive 11 sessions, the participants will go to the maintenance phase of intervention, which involves telephone consultation sessions on a monthly basis for three months. The maintenance telephone consultation will last no more than 20 min per consultation.

#### Train the trainer

In order to build the sustainability and increase intervention fidelity of the ILSM program, this research uses train the trainer model. The research team will go to each site to train four project field officers in ILSM intervention with lifestyle intervention skills (e.g. ILSM protocols, intervention research, and communication) to provide the ILSM program (Train the trainer model of care) based on the facilitating video and the guidebooks developed by the research team. Their responsibilities will include: (1) Help to identify the eligible participants and recruit the participants; (2) Provide ILSM for the participants; (3) Make the telephone reminders and the site arrangement for the four time-points measurements. Standardization of intervention delivery is assessed by use of the facilitator’s guidebook. Motivational interviewing principles are used with all of the sessions.

#### Usual care (Control group)

Because women with prior GDM are at high risk for T2DM, it is not ethical to provide no treatment. Currently, the clinical guidelines for T2DM prevention include providing information for T2DM prevention to high risk populations, including lifestyle modification and diabetes screening (38). The usual care provided in this proposed project will utilize current clinical guideline and recommendations for T2DM prevention. Each participant will receive the same brochure of diabetes prevention education information as the ILSM group. However, participants in the control group will not have group sessions and phone consultations.

Similar to the ILSM group, four local health workers in the usual care group will be trained as the project field officers. Their responsibilities will include: (1) identify the eligible participants and recruit the participants; (2) ensure participants in the usual care group will receive general oral and written information about awareness of diabetes, information about the importance of dietary modification and physical activity, and suggestions of diabetes screening every three years at the baseline assessment; (3) make the telephone reminders and the site arrangement for the four time-points assessments. The participants will complete the same measurement at the same time intervals at the ILSM groups.

Upon completion of the 18-month study, participants from either the control group or the ILSM group will receive a 100 RMB gift certificate as “thank you” for participation and to sustain their involvement in the study. We will send all participants in this study a birthday message for her birthday. The study flowchart was displayed in Fig. 2.

**Fig. 2 Fig2:**
[figure not shown]
Flowchart of the study

### Variables and measurements

Each measure was selected to operationalize theoretical constructs and has been used in Chinese rural populations and demonstrated adequate psychometric properties. The research team will measure outcomes at baseline (T-0), immediately after main ILSM at 3 months (T-1), immediately post intervention at 6 months (T-2) and 18-month post intervention (T-3), which are displayed in Table 3. All measures employed in the proposed study will be collected by trained research assistants who are blinded to the group assignments.

**Table 3 Tab3:** Variables and measures collected at evaluation time points

Variables		Data source	Measures	Time point			
				T-0	T-1	T-2	T-3
Covariates	Socio-demographic factors	Survey & medical record	Age, marital status, education level, occupation, annual household income, and ethnicity.	×			
	Health characteristics		Smoking status, alcohol consumption, pre-pregnancy BMI, gestational weight gain, parental history of diabetes, GDM, and cardiovascular disease.	×			
	Clinical characteristics		Gestational week and age at the diagnosis of GDM, numbers of pregnancies, history of pregnancy complications, birth weight of children, gestation week at delivery, treatment for GDM.	×			
Weight-related Behaviors	Dietary intake	Survey	Food frequency questionnaire [40]	×	×	×	×
	Physical activities		International Physical Activity Questionnaire (Short version) [41]	×	×	×	×
Psychosocial Variables	Self-efficacy: the belief in one’s effectiveness in performing specific tasks.	Survey	Self-rated abilities for health practices scale [42]	×	×	×	×
	Perceived stress: the feelings or thoughts that an individual has about how much stress they are under over a given time period.		Perceived Stress Scale [43]	×	×	×	×
	Social support: the perception and actuality that one is cared for.		Social Support Rating Scale [44]	×	×	×	×
	Quality of life: the general well-being of individuals		The World Health Organization Quality of Life Scale-BREF [45]	×	×	×	×
Physiological outcomes	Insulin resistance: a physiological condition in which cells fail to respond to the normal actions of the hormone insulin	Spot measuring	OGTT-2 h	×	×	×	×
	T2DM screening & development		HbA1c ≥6.5% is considered T2DM.				
Weight-related measures	BMI & Waist circumference	Spot measuring	BMI is weight/height^2^ (Kg/m^2^)	×	×	×	×
Cardiovascular disease risk	Blood Pressure	Spot measuring	Systolic blood pressure, Diastolic blood pressure	×	×	×	×
Cost-effectiveness Outcomes	The costs falling on health and social care systems	Survey & Medical records	A PI-designed questionnaire	×	×	×	×
	The costs falling on individuals and families						
	The effectiveness outcomes		The above clinical and physiological measurements	×	×	×	×

Personal and family characteristics (Covariates): Socio-demographic factors, health characteristics, and clinical characteristics will be collected. Weight-related behaviors (Secondary outcome measures): Two separate questionnaires on changes in dietary intake and physical activity habits will be assessed. Psychosocial variables (Secondary outcome measures): self-efficacy, perceived stress, social support, and quality of life will be measured, the operation definition of which are displayed in Table 3. Physiological outcomes: BMI and waist circumference will be measured as weight-related variables, while blood pressure will be evaluated as cardiovascular disease risk. The biomarkers of insulin resistance will include glucose values on the oral 75 g glucose 2 h post-load glucose tolerance test (OGTT-2 h). T2DM screening and development will be measured by HbA1c. BMI, OGTT-2 h, and HbA1c are the primary outcome measures.

Cost-effectiveness outcomes: We will measure the costs accruing to the health and social care system and to individuals and families for the ILSM program and for health care (in order to assess the effects of ILSM), including inpatient and ambulatory care, medicines, personnel costs to deliver the ILSM, and other procedures and treatments. For the effectiveness component, we will rely on clinical and physiological measurements noted above. These two elements permit cost-effectiveness calculations. In addition, we will assess the costs falling on individuals and families for non-medical costs (travel, child-minding, and time/lost income), which will be used in a secondary cost-effectiveness calculation.

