### Study participants

Participants will be invited to participate in this study if they meet the following inclusion criteria: 1) Women with a history of GDM; 18 years or older; 2) at least six weeks post-partum at the beginning of the study; 3) intend to live in the research counties for at least 3 years; 3) intend to seek primary maternal and child health care in the research sites for at least 3 years; 4) have telephone-access either from family members, friends, or neighbors; 5) be able to speak Chinese.

Exclusion criteria: 1) Planning to become pregnant within the next three years; 2) Currently pregnant; 3) Diabetes diagnosed before pregnancy or after delivery; 4) Medications that influence glucose metabolism; 5) Multiple pregnancies (three or more); 6) Physical or cognitive disability; 7) Current addictive drug abuse; 8) Severe psychiatric disorders.

The power calculations for multivariate procedures are generally more complex and require a priori assumptions that are difficult to verify. Using GPower3.1 we calculated the power of tests of odds ratios in logistic regressions comparing threshold values of OGTT 2 h and HbA1c in ILSM versus control samples. For odds ratios of 0.667 (odds of insulin resistance above threshold in the ILSM groups versus the equal odds in the control group), a combined sample of *N* = 256, relatively high correlations between the other covariates, and a probability of a Type 1 error of .05, the power of the test against null hypothesis of that the odds ratio is 1.0 is about 0.71.

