### Intervention

Participants will be enrolled in the study for a total of 18 months. For both groups, the assessment time points include at the beginning of the study (T-0), at 3, 6, and 18 months after baseline assessment (T-1, T-2, and T-3). The 3-, 6- and 18-month after baseline assessment include questionnaires completion as T-0 and the physical assessment (e.g. BMI, waist circumference, blood pressure, OGTT-2 h, and HbA1c). If the OGTT-2 h is abnormal at any time point, the next time point the participants will not assess OGTT-2 h. The timeline of the intervention activities for ILSM group and control group is showed in Table 1.

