### Statistical analysis

Our analysis plan focuses on comparisons between ILSM and control groups with respect to key intermediate outcomes: HbA1c (%),OGTT 2 h (mmol/L), BMI, waist circumference (in cm), SBP and DBP (mmHg), and measures of dietary intake, physical activity, self-efficacy, and social support. The comparisons take the form of 1) simple differences of average values of change (for quantitative characteristics) from baseline to follow-up measures or turnover tables showing baseline versus follow-up (for data organized into categories) and 2) more complex analyses based on multivariate methods that incorporate adjustment for clustering and covariates.

We will assess cost-effectiveness using an existing spreadsheet-based simulation model called GeDiForCE (Gestational Diabetes Formulas for Cost-Effectiveness), developed by UCSF and Health Strategies International with funding from NovoNordisk. This model uses a decision tree and input values from published studies to portray the risks of T2DM with and without a post-partum intervention. In this study, we will adjust input values to reflect data collected on costs and effectiveness. The cost data described above can be directly incorporated into the model. The effectiveness data will be calculated from the clinical and physiological outcomes above. We will directly incorporate incidence of T2DM. However, due to the relatively short follow-up time frame, as compared with a delay of ten or more years for the incidence of T2DM, we will also use short-term changes in physiological indicators (such as OGTT-2 h and HbA1c) in a simple risk-of-progression model in order to predict long-term effects on incidence of T2DM. This progression model will be calibrated to empirical evidence on the progression from glucose intolerance to T2DM.

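### T2DM development rests on trial-visit HbA1c alone, so cases seen only on OGTT-2 h or diagnosed and treated elsewhere go uncounted; the direction of the bias is uncertain

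*Protocol article*

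**What the plan says.** T2DM development comes first among the outcomes in the primary purpose (end of Background). Under Variables and measurements, "T2DM screening and development will be measured by HbA1c", and Table 3 gives the only criterion: "HbA1c ≥6.5% is considered T2DM". OGTT-2 h is listed as the biomarker of insulin resistance, not as a criterion for T2DM. The same section states that "BMI, OGTT-2 h, and HbA1c are the primary outcome measures".

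Other passages bear on this:
- **Intervention:** visits are at baseline and at 3, 6 and 18 months after it. "If the OGTT-2 h is abnormal at any time point, the next time point the participants will not assess OGTT-2 h".
- **Study participants:** the exclusions include diabetes diagnosed before pregnancy or after delivery, and "Medications that influence glucose metabolism". Neither has a stated role after entry.
- **Table 3 and the cost-effectiveness paragraph:** medicines and inpatient and ambulatory care are collected through surveys and medical records at all four time points, for costs. The effectiveness side is to rely on the clinical and physiological measurements.
- **Statistical analysis:** for the cost-effectiveness model, "We will directly incorporate incidence of T2DM".
- **Screening advice:** the sixth ILSM session stresses T2DM screening every six months (Table 2). Usual care suggests it every three years.

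**The concern.** The stated rule leaves out two kinds of case that the trial could see. One is the woman whose OGTT-2 h reaches the diabetes range while her HbA1c stays below 6.5%. The other is the woman diagnosed outside the trial and treated, whose HbA1c is below 6.5% when she attends. Both are recorded as not having developed T2DM.

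At stake are the incidence comparison and, through it, the cost per T2DM case averted. Few events are expected, so a handful of misclassified women can change the result. Outside diagnosis may also differ by arm, because the two arms are told to screen at different intervals.

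**Working it through.** The plan gives no figure for this point, so there is nothing to reproduce. The main check is textual; the arithmetic only shows a plausible scale.

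**1. Who is counted under the stated rule**

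| Woman without T2DM on HbA1c at entry | Counted as T2DM? |
|---|---|
| HbA1c at or above 6.5% at T-1, T-2 or T-3, whatever follows | Yes |
| OGTT-2 h in the diabetes range, never at or above 6.5% at a visit | No |
| Diagnosed and treated elsewhere, never at or above 6.5% at a visit | No |

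The OGTT skip rule adds to this. After an abnormal OGTT-2 h at T-2 there is none at T-3, so at T-3 only HbA1c could identify her.

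**2. Time without a trial test.** With visits at 3, 6 and 18 months after baseline, 12 of the 18 months fall between T-2 and T-3. With a constant hazard (assumption), 12/18 = 0.67 of new cases arise there.

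**3. Expected cases.** The Background cites an incidence of 10 to 40% over 1 to 10 years after GDM. Reading both ends as 10-year risks (assumption), 18 months is 0.15 of that period:
- Low: 256 × (1 − 0.90^0.15) = 4.0
- High: 256 × (1 − 0.60^0.15) = 18.9

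**4. Cases lost to outside diagnosis and treatment.** Share lost = 0.67 × share diagnosed elsewhere × share of those below 6.5% on treatment at T-3. The last two inputs are assumptions.

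| Diagnosed elsewhere | Below 6.5% on treatment | Share lost | Of 4.0 cases | Of 18.9 cases |
|---|---|---|---|---|
| 30% | 50% | 10% | 0.4 | 1.9 |
| 50% | 70% | 23% | 0.9 | 4.4 |

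Women identified only by OGTT-2 h are additional. The document gives no basis for estimating their number.

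**5. Direction.** Take an assumed control risk of 10% and, for illustration, the odds ratio of 0.667 from the sample-size paragraph. The true ILSM risk is then 6.9%. Multiply each arm's risk by (1 − share masked):

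| True OR | Masked, ILSM | Masked, control | Observed risks, ILSM and control | Observed OR |
|---|---|---|---|---|
| 0.667 | 20% | 20% | 5.52%, 8% | 0.672 |
| 0.667 | 40% | 40% | 4.14%, 6% | 0.677 |
| 0.667 | 40% | 20% | 4.14%, 8% | 0.497 |
| 0.667 | 20% | 40% | 5.52%, 6% | 0.915 |
| 1 | 40% | 20% | 6%, 8% | about 0.73 |

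Equal masking hardly moves the odds ratio but does shrink the absolute difference. With 128 women per arm (assumption), true cases are 12.8 and 8.8, so 4.0 are averted. At 40% masking in both arms this becomes 7.7 − 5.3 = 2.4. Unequal masking biases the odds ratio either way.

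**The case against.** HbA1c at trial visits is a defensible choice: it is objective, taken on one schedule in both arms, and collected by blinded assistants. Counting outside diagnoses in the main definition would let six-monthly against three-yearly screening advice drive the event count. This stands, and it is why outside diagnoses belong in a separate analysis. It does not apply to OGTT-2 h, which shares the visits and the blinding.

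The declared primary measures are BMI, OGTT-2 h and HbA1c, and the Discussion concedes that an effect on long-term incidence will be hard to show. The cost-effectiveness model also uses short-term changes in OGTT-2 h and HbA1c. These points limit the consequence, but incidence still enters the model directly.

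The upper scenario may be high. The Background puts undiagnosed T2DM in rural areas at 70.5%, hence 29.5% diagnosed. With that and 70% below 6.5% on treatment, the loss is 0.67 × 0.295 × 0.70 = about 14%, or 0.6 to 2.6 cases.

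Two stronger readings are tempting but unsupported:
- **Treated values are analysed at face value as good outcomes.** The article is silent on values after medication starts, and that commonly sits in an analysis plan. It also does not say that an abnormal on-study OGTT leads to diagnosis or treatment; referral is stated only at screening. This is a risk to guard against, not a stated error.
- **The bias is towards no effect because most lost cases are controls.** More frequent screening advice in ILSM could instead remove more ILSM cases and favour the intervention.

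**Conclusion.** The concern holds as a point about a fixed outcome definition. T2DM development depends on visit HbA1c alone, and neither OGTT-2 h nor the medicines and care data has a stated role in finding cases. Only women never at or above 6.5% at a trial visit are missed.

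The size cannot be derived from the document. About 0.4 to 4.4 of roughly 4 to 19 expected cases would be lost to outside treatment. This assumes a constant hazard, the cited 10 to 40% read as 10-year risks, 30 to 50% of cases in the gap diagnosed elsewhere, and 50 to 70% of those below 6.5% on treatment. The direction is uncertain. The point affects the incidence comparison and the cost-effectiveness result; it does not by itself show that the comparisons of BMI, OGTT-2 h or HbA1c are wrong.

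**What to change.** 1. Define T2DM development as the first trial-visit HbA1c at or above 6.5%, or OGTT-2 h at or above the diabetes threshold the sponsor already uses. Exclude from incident cases women already in that range at T-0. State what an abnormal OGTT-2 h means, and reconcile the definition with the rule that skips the next OGTT after an abnormal one.
2. Add an analysis that also counts a physician diagnosis or the start of glucose-lowering medication, taken from the survey and medical-record data already collected. Report it beside the visit-based and HbA1c-only counts, and note that unequal screening advice can drive outside diagnoses.
3. Add a sensitivity analysis of HbA1c, OGTT-2 h and BMI that does not take values after the start of glucose-lowering medication at face value. This needs medication start dates at T-1 to T-3.
4. Run the cost-effectiveness model under each of these incidence definitions.

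The cost is a change of wording, a little more analysis work, and more than one incidence figure to report.

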### Statistical analysis

Our analysis plan focuses on comparisons between ILSM and control groups with respect to key intermediate outcomes: HbA1c (%),OGTT 2 h (mmol/L), BMI, waist circumference (in cm), SBP and DBP (mmHg), and measures of dietary intake, physical activity, self-efficacy, and social support. The comparisons take the form of 1) simple differences of average values of change (for quantitative characteristics) from baseline to follow-up measures or turnover tables showing baseline versus follow-up (for data organized into categories) and 2) more complex analyses based on multivariate methods that incorporate adjustment for clustering and covariates.

We will assess cost-effectiveness using an existing spreadsheet-based simulation model called GeDiForCE (Gestational Diabetes Formulas for Cost-Effectiveness), developed by UCSF and Health Strategies International with funding from NovoNordisk. This model uses a decision tree and input values from published studies to portray the risks of T2DM with and without a post-partum intervention. In this study, we will adjust input values to reflect data collected on costs and effectiveness. The cost data described above can be directly incorporated into the model. The effectiveness data will be calculated from the clinical and physiological outcomes above. We will directly incorporate incidence of T2DM. However, due to the relatively short follow-up time frame, as compared with a delay of ten or more years for the incidence of T2DM, we will also use short-term changes in physiological indicators (such as OGTT-2 h and HbA1c) in a simple risk-of-progression model in order to predict long-term effects on incidence of T2DM. This progression model will be calibrated to empirical evidence on the progression from glucose intolerance to T2DM.

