Many interventions, including lifestyle and pharmacotherapy interventions, have been developed to prevent T2DM. Lifestyle interventions, in particular, have demonstrated potential efficacy in reducing T2DM incidence and may be superior to pharmacological retreatment [12]. A recent systematic review [11] examined the efficacy of lifestyle interventions in decreasing T2DM for women with GDM using randomized clinical trials found that the majority of the trials (92%) targeted women in an urban setting [13–23] and the results suggest that postpartum lifestyle interventions for women with GDM history can decrease T2DM risk significantly on the short-term follow up. However, these studies are limited to pilot or feasibility studies and only three studies were conducted in China and all of them focused on women in urban cities [15, 16, 21].

Although about half of the population (700 million people) resides in rural areas in China [24], there is a huge rural-urban gap of income, education and health resources, with the living situation in urban areas being much better than that in the rural areas [25]. People in rural areas are also suffering from unhealthy lifestyle practices as they are more likely to smoke, exercise less frequently, and have lower health literacy than their urban counterparts [26, 27].

Women living in rural area in China practice more traditional Chinese customs of a “sitting month” during postpartum period that include more sedentary behavior and increased consumption of high-calories, high-fat, and high-protein food intake during the first month [28]. These traditional practices might make Chinese women miss the optimal period for weight loss and healthy lifestyle change [29]. Other issues could increase risk for T2DM in women in rural areas include inadequate in-service training, staff shortages, poor resource distribution, and transportation difficulties which create health inequality in rural areas in China [30]. Thus, diabetes prevention interventions with lifestyle modification for rural Chinese women with prior GDM are urgently needed.

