### Recruitment

Recruitment of potential participants will occur by a review of medical records of the women who delivered babies in the research sites. Potential participants who meet inclusion criteria will receive a phone call from a trained project field officer to explain the purpose of the study and assess interest in participation. The trained project field officers who are physicians or nurses working in the research sites will be recruited from the research sites.

The project field officers will confirm their eligibility and obtain consent. As part of eligibility assessment, all interested study participants will undergo postpartum HbA1c testing to make sure the potential subjects do not have T2DM. If HbA1c suggests T2DM, the participant will not be eligible to participate in the study. However, she will be referred to the physicians for further T2DM diagnosis and treatment. If HbA1c are within normal limits, the women will be recruited. Women who do not meet the inclusion criteria will be thanked for their time. We will also document reasons from mothers who decline to participate in the study.

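### Neither the unadjusted change-score comparison nor the adjusted analysis is named primary, and the listed covariates omit the baseline outcome value and time since delivery

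*Protocol article*

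**What the plan says.** The Statistical analysis section of the protocol article lists HbA1c, OGTT-2 h, BMI, waist circumference, blood pressure and the behavioural and psychosocial scores, and gives two forms of comparison for them:

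- **Form 1**, for quantitative outcomes: "simple differences of average values of change (for quantitative characteristics) from baseline to follow-up measures".
- **Form 2**: "more complex analyses based on multivariate methods that incorporate adjustment for clustering and covariates".

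Adjustment for clustering is attached to form 2 only. No sentence says which form carries the conclusion. Under Variables and measurements, "BMI, OGTT-2 h, and HbA1c are the primary outcome measures".

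Table 3 has a block labelled as covariates. Its socio-demographic row reads "Age, marital status, education level, occupation, annual household income, and ethnicity". The other two rows cover health characteristics (including pre-pregnancy BMI and gestational weight gain) and clinical characteristics (including gestational week and age at GDM diagnosis, and gestation week at delivery). The T-0 value of the outcome and time since delivery appear in none of the three rows.

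The Study participants section requires women to be "at least six weeks post-partum at the beginning of the study" and states no upper limit. The Methods section places randomisation at town level within two counties.

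**The concern.** Form 1 sets the coefficient of the baseline value at 1. When baseline and follow-up correlate imperfectly, that is the wrong weight. It adds noise, and it turns a chance difference between the arms at T-0 into an apparent difference in change, because the arm that starts higher tends to fall further without treatment. The women in a town enter an arm together, so a form that makes no allowance for town also misstates the standard error.

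Form 2 could deal with all of this. However, it is not named primary, and the listed covariates lack the one variable that would do most of the work, the T-0 value of the same outcome.

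Time since delivery is a second gap. Women may enter at six weeks or much later. The Background treats the period after birth as distinctive for weight: "These traditional practices might make Chinese women miss the optimal period for weight loss and healthy lifestyle change". If the arms differ in weeks since delivery, a BMI comparison that ignores it may mix that difference with the effect of the programme.

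**Working it through.** **1. The plan's own figure.** The article states no power, SD or correlation for any quantitative outcome. Its one power figure, about 0.71 (Study participants), is for a logistic regression on thresholded OGTT-2 h and HbA1c. It does not reproduce as a plain two-arm comparison. Taking 128 women per arm (an even split is assumed), control odds of 1 (proportion 0.50) and odds ratio 0.667 gives 0.667/1.667 = 0.40 in the ILSM arm, with power 0.36 two-sided or 0.48 one-sided. That is a separate matter, and nothing below rests on 0.71.

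**2. Availability of baseline values.** Table 3 marks OGTT-2 h and BMI at T-0. For HbA1c, the Recruitment section says "all interested study participants will undergo postpartum HbA1c testing to make sure the potential subjects do not have T2DM". A pre-intervention value therefore exists for each primary outcome.

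**3. Precision.** Assume equal variance σ² at both times and correlation r.

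- Change score: Var = σ² + σ² − 2rσ² = 2(1−r)σ².
- Follow-up adjusted for baseline: Var = (1−r²)σ².
- Ratio: (1−r)(1+r) / [2(1−r)] = (1+r)/2.

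The article gives no r, so it is varied:

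| Assumed r | Variance ratio | Women needed with baseline adjustment to match 256 with change scores | Power with baseline adjustment where the change-score test has 80% |
|---|---|---|---|
| 0.3 | 0.65 | 256 × 0.65 = 166.4, so 167 | 94% |
| 0.5 | 0.75 | 256 × 0.75 = 192 | 90% |
| 0.7 | 0.85 | 256 × 0.85 = 217.6, so 218 | 86% |
| 0.9 | 0.95 | 256 × 0.95 = 243.2, so 244 | 82% |

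The last column is Φ[(1.960 + 0.842)/√((1+r)/2) − 1.960], two-sided at 5%. For r = 0.5: 2.802/0.866 = 3.235; 3.235 − 1.960 = 1.275; Φ(1.275) = 0.90. All figures are at individual level. No design effect is applied, because the article gives no intracluster correlation and no number of towns.

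**4. Chance imbalance.** If the arms differ by d SD at T-0, the expected change-score contrast shifts by −(1−r)d SD. Per 1 SD of imbalance that is −0.7, −0.5, −0.3 and −0.1 SD for r = 0.3, 0.5, 0.7 and 0.9. As an illustration, with d = 0.2 and r = 0.5 the shift is −0.5 × 0.2 = −0.10 SD, which flatters the arm that started higher.

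**5. Time since delivery.** The lower limit is six weeks. No upper limit is stated, but the Discussion says GDM screening was not widely done or recorded locally until 2015, so only women with recent GDM can be reached. That narrows the range without closing it. Age and age at GDM diagnosis are both collected, and their difference is a proxy, but a coarse one if both are in whole years. Recruitment is by review of the records of women who delivered at the sites, and the delivery date should be there.

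**The case against.** The strongest reply is that form 2 already promises adjustment for clustering and covariates. In a town-randomised trial, form 1 then reads naturally as the descriptive comparison, and the contents of form 2 are the sort of detail that an article leaves to its analysis plan. Table 3 lists what is collected and does not specify a regression. Part of this stands: a reader might infer that outcomes are compared only as raw change, and the document does not support that. What the reply does not answer is that the article puts the change score first, makes neither form primary, and prints an itemised covariate list without the baseline outcome.

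Four other inferences are tempting but go too far:

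- **BMI drifts at a known rate after delivery.** The Background describes customs of the first month, before the earliest entry, and gives no length for its favourable period and no rate of change. It makes time since delivery a sensible covariate and does not quantify its effect.
- **Imbalance is likely because there are few towns.** The number of towns is not stated.
- **Baseline adjustment removes imbalance.** It adjusts for imbalance in measured variables. Field officers recruit separately for each arm (Train the trainer; Usual care), and neither change scores nor baseline adjustment corrects for selection arising there.
- **The gain would repair the stated power of 0.71.** That test uses thresholded outcomes, to which the variance ratio does not apply.

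**Conclusion.** The point holds in limited form. The article states an unadjusted change-score comparison, does not rank it below the adjusted one, and lists covariates without the baseline outcome or time since delivery. A better method is available on data already planned.

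The direction is firm: with equal variances, baseline adjustment is more precise than the change score for any r below 1. The size is not firm. The individual-level variance saving is 35% at r = 0.3 and 5% at r = 0.9, and it may differ between outcomes. With town-level randomisation and no intracluster correlation given, these percentages should not be read as an exact equivalent in women. The shift from chance imbalance, −(1−r) SD per SD, also depends on the assumed r. No effect of time since delivery can be calculated from the article; the case for including it rests on the open-ended entry window.

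**What to change.** In the Statistical analysis section, name one primary analysis for each quantitative outcome: a model of the follow-up value on arm, the T-0 value of the same outcome and county, accounting for town (for example, a random effect for town). Label the raw mean change as descriptive.

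Add weeks since delivery at T-0 to the covariates in Table 3 and prespecify it in that model, derived from the delivery records reviewed for recruitment.

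State that this adjusts only for the measured variables. It does not correct for unmeasured differences between towns or selection by arm-specific recruiters, and it does not supply the OGTT-2 h values that are not taken at the visit after an abnormal result.

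The cost is a few lines of analysis text and one date-derived variable from records already reviewed. No extra visit, test or participant is needed.
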